### emoTICare

The *emoTICare* program engages users through a serious game aimed at developing socio-emotional skills and promoting physical and emotional health in adolescents with T1DM. This graphic adventure game consists of a time-travel journey across different parts of the world and various historical periods. Using the DAMIP model, a series of playable areas were developed to address the key factors that promote adaptive adjustment to chronic illness, specifically tailored to T1DM in the adolescent population.

According to the principles of *serious games*, players need to experience a certain level of immersion, as this increases the likelihood of changing beliefs and attitudes in real life [52]. To achieve this, a narrative context was established to enhance immersion, supported by a fictional storyline and well-defined goals that guide the player through the challenges necessary to complete the intervention.

After reviewing possible genres and settings and consulting the target population about their preferences, it was concluded that the storyline and setting should feature a graphic adventure incorporating time travel mechanics.

Initially, the player awakens disoriented in an unfamiliar place, which turns out to be the Temporal Control Center. Here, they meet an Artificial Intelligence called *Alura*, who oversees the center and will serve as their guide to help them understand the game mechanics.

*Alura* explains that a temporal rupture has occurred, causing the clock of time to stop, and its cores have been scattered in unknown places, altering the world as it was known. From this point on, the character embarks on a space-time adventure to recover all the cores and repair the clock (for more detailed information on emoTICare, access the S1 File).

Throughout the game, the player will travel to six distinct areas: Egypt (Psychoeducation Area), Venice (Emotional Awareness Area), the Amazon (Emotional Regulation Area), *NewGlobal* (Cognitive Coping Area), Petra (Identity Area), and India (Social and Communication Skills Area).

Each of these areas will focus on one of the indicators of quality of life in adolescents specified in our theoretical model, as follows:

#### Area 1: Psychoeducation about the disease.

This area focuses on the physical well-being of the user and is designed to provide psychoeducation on T1DM, ensuring users gain a deeper understanding of their illness, which in turn promotes better adjustment. This area comprises four main tasks: Use of the Glucometer, Dietary Control, Physical Exercise, and Basic Knowledge of Type 1 Diabetes.

#### Area 2: Emotional awareness.

In this area, the foundation for the user’s emotional well-being is established. First, users must become aware of both their own emotions and those of others. Therefore, this area covers the primary definitions and functions of basic emotions (joy, fear, etc.) and complex emotions (love, shame, etc.), as well as the recognition and identification of these emotions in themselves and others. It consists of five tasks: Utility and Definition of Emotions, Identification of Emotions, Definition of Complex Emotions, Emotional Vocabulary, and Emotions in Context.

#### Area 3: Emotional regulation.

This area continues to focus on the user’s emotional well-being while introducing strategies for emotional coping. It emphasizes the regulation and control of various emotions, along with relaxation techniques. This area consists of two main tasks (Cognitive Relaxation/Mindfulness and Muscle Relaxation) and one ongoing task (Knowledge and Practice of Short-Term Stress Management Techniques). The user will learn seven short-term stress control strategies and determine which to employ in response to various situations encountered throughout the area. The strategies include: Abdominal Breathing, Internal Distraction, External Distraction, Internal Dialogue, Cognitive Discharge, Motor Discharge, and Environmental Change. Ultimately, the aim is to provide the user with effective tools for managing stress in real-life situations.

#### Area 4: Cognitive coping.

After addressing emotional well-being and coping strategies, users advance to learning tools for cognitive coping in potentially stressful situations. This area comprises three essential tasks: Problem-Solving, Self-Instruction Training, and Thought Stopping and Cognitive Restructuring.

#### Area 5: Identity.

This area focuses on the user’s self-perception and the values that define them, aiming to highlight concepts such as self-esteem, self-concept, self-image, and self-awareness. The tasks in this area are: Personal Qualities, Values, Self-Reflection Questions, and Shadow Test.

#### Area 6: Social development and communication.

Finally, the last area centers on the user’s social skills and how they express and present themselves to others. Concepts such as assertiveness, conflict coping styles, and barriers to effective communication between two individuals will be explored. The four tasks in this area are: Positive Communication, Active Listening, Assertiveness and Social Skills, and Conflict Resolution.

### Minigames

In addition to the areas that users will progressively access throughout the intervention, specific tasks have been developed for each area. These tasks aim to ensure users continue practicing the acquired techniques and reinforce their learning. The first five areas will feature a repeatable “minigame” that users can play as many times as they like while waiting for the next area to become available. The minigames are: Knowledge of Diabetes, Emotion Identification, Relaxation Techniques, Key Point Analysis, and Changing Irrational Beliefs about Identity.

### Assessment tools

#### Clinical and sociodemographic variables.

Sociodemographic variables such as gender, age, nationality, previous contact with psychology professionals, and reason for consultation will be assessed using an ad-hoc record after informed consent has been obtained.

Additionally, to gather relevant data related to the illness and its impact on adolescents, an ad-hoc record will collect the following medical variables:

Glycated Hemoglobin (HbA1c)Cause and number of hospitalizations due to diabetesMonths since the onset of the diseasePerceived difficulty due to the illnessSpecific aspects of diabetes causing the most difficultyPresence of other medical conditionsPresence of psychological disordersType of medical treatment received for T1DMPhysical consequences of T1DM

#### Psychological variables.

To assess the **perceived threat of disease**, the ***Brief Illness Perception Questionnaire*** (BIP-Q) by Broadbent et al. [65], adapted for Spanish adolescents ([66], will be used. This questionnaire includes five Likert-type items (0–10), along with an open-response item. It evaluates cognition through subscales for *Consequences of the Disease*, *Duration of the Disease*, and *Identity*, as well as emotional aspects through subscales for *Concern about the Disease* and E*motional Impact of the Disease*. The open-ended item assesses the causal representation of the disease. The adapted version shows satisfactory psychometric properties, with reliability of α = 0.76 and good internal validity.

**Health-related quality of life** will be measured using the validated Spanish version of the ***KIDSCREEN-27*** questionnaire [67]. This instrument consists of 27 Likert-type items (1–5), divided into five dimensions: *Physical Well-Being*, *Psychological Well-Being*, *Autonomy and Parent Relations*, *Social Support and Peers*, and *School Environment*. The original version of the questionnaire has good internal validity and high Cronbach’s alpha scores above 0.70 in the five dimensions. The Spanish version also demonstrates acceptable reliability and construct validity, with internal consistency scores equal to or greater than 0.70 across all dimensions.

**Psychopathology** will be assessed using the ***Strengths and Difficulties Questionnaire*** (SDQ) by Goodman [68], validated in Spanish by Ortuño-Sierra et al. [69]. This tool evaluates emotional and behavioral symptoms, as well as prosocial behavior in children and adolescents. It consists of 25 Likert-type items (0–3), grouped into five scales: *Emotional Symptoms*, *Behavioral Problems*, *Hyperactivity*, *Peer Problems*, and *Prosocial Behavior*. The first four scales assess behavioral and emotional difficulties, while the fifth focuses on positive social behaviors. The sum of the first four scales (excluding *Prosocial Behavior*) forms a sixth scale, *Total Difficulties*. The self-report version of the questionnaire has demonstrated adequate internal consistency in most studies. In its adapted Spanish version [69], internal consistency scores for the various subscales range from 0.58 (*Behavioral Problems*) to 0.71 (*Emotional Symptoms*).

To assess **social skills** and **communication abilities** in adolescents, the latest validated version of the *Social Skills Questionnaire* (CHASO) by Caballo et al. [70] will be used. It comprises 40 Likert-type items (1–5) and evaluates 10 skills: *Interacting with Strangers*, *Expressing Positive Feelings*, *Facing Criticism*, *Interacting with People Who Attract Me*, *Staying Calm in the Face of Criticism*, *Public Speaking/Interacting with Superiors*, *Dealing with Embarrassment*, *Defending One’s Rights*, *Apologizing*, and *Rejecting Requests*. Psychometric properties show a reliability of α = 0.88 and a Guttman reliability coefficient of 0.86.

**Emotional awareness** will be evaluated using the ***Emotion Awareness Questionnaire*** (EAQ-30) by Rieffe et al. [71], adapted into Spanish by Samper-García et al. [72]. This 30-item Likert-type questionnaire (1–3) identifies how adolescents perceive their emotions, the intensity with which they feel them, and their ability to express them. It comprises six subscales: *Emotion Differentiation*, *Verbal Sharing*, *Not Hiding Emotions*, *Body Awareness*, *Emotion Analysis*, and *Attention to Others’ Emotions*. The validation of the scale in a Spanish sample yielded a reliability score of α = 0.74.

To evaluate **coping and problem-solving skills** in adolescents with T1DM, the short version of the ***Social Problem Solving Inventory – Revised*** (SPSI-R) by Zurilla and Nezu [73] will be used. This questionnaire measures cognitive, emotional, and behavioral responses to everyday problems or difficulties. It consists of 25 Likert-type items, grouped into five dimensions: *Rational Problem Solving* (RPS), *Avoidant Style* (AS), *Impulsive Style* (IS), *Positive Problem Orientation* (PPO), and *Negative Problem Orientation* (NPO). The questionnaire has demonstrated adequate psychometric properties [74], with reliability scores for the five dimensions as follows: RPS (α = 0.76), AS (α = 0.74), IS (α = 0.74), PPO (α = 0.67), and NPO (α = 0.76).

**Resilience** will be measured using the 10-item ***Connor-Davidson Resilience Scale*** (CD-RISC) [75], validated in Spanish by Notario-Pacheco et al. [76]. This scale uses Likert-type items (0–4) and has demonstrated strong psychometric properties (α = 0.85).

Adolescent **self-concept** will be assessed using the latest version of the ***Garley Self-Concept Questionnaire*** (CAG) by García Torres [77]. This instrument aims to measure self-concept from a multidimensional perspective in adolescents. It consists of 48 Likert-type items, providing a global self-concept score, and is divided into six subdimensions: *Physical Self-Concept*, *Social Acceptance, Family Self-Concept*, *Intellectual Self-Concept*, *Self-Evaluation*, and *Sense of Control*. The questionnaire shows adequate psychometric properties for both the global score (α = 0.87) and the subscales.

Lastly, as a control variable, the ***Oviedo Infrequency Response Scale*** will be administered, developed by Fonseca-Pedrero et al. [78]. This scale consists of 12 Likert-type items (1–5) that are distributed throughout the questionnaire at key points. The items are organized into three groups of four, coded according to the questionnaire variable in which they are integrated. If a subject answers three or more items incorrectly, their questionnaire responses will be invalidated.

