## Materials and methods

### Study design

A clinical longitudinal experimental design with inter-subject comparisons was employed, with the aim of comparing an experimental group (i.e., individuals receiving psychological treatment) and a control group on the waiting list (i.e., those without treatment) at three time points: before treatment (T1), and two post-treatment time points (T2, T3). The control group hasn’t any alternative activities or exposure to placebo-like interactions. Furthermore, an intra-subject analysis was conducted by comparing repeated measures to observe changes within the same individuals before (with pre-treatment measurements, T1), after 6 weeks (T2, in the control group and post-treatment in the experimental group), 6 months after T2 (T3, in the control group and post-treatment in the experimental group).

Initially, immediately after completing the informed consent online, a first evaluation will be conducted for all participants (T1), covering the main areas that constitute the psycho-emotional state of the participants. Following this first evaluation, participants in the experimental group will engage in six weeks of gameplay, with each week dedicated to completing one mission of *emoTICare*. At the six-week mark after the initial evaluation, and immediately following the completion of the *emoTICare* application by participants in the experimental group, a second evaluation (T2) of all participating adolescents (control and experimental groups) will take place. Following a period of six months from T2, a subsequent measurement, designated T3, will be conducted in all participants.

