The phase encompassing the evaluation of the variables of interest, T1-T2-T3, will take place through the survey platform of the Universitat de València, Limesurvey, from September 2024 to the end of February of 2027. The response platform for the questionnaire battery includes a consent form for anonymous participation in the study. In this platform, informed consent will be obtained from the parents or legal guardians of the participants, as well as from the minors themselves, ensuring that all are informed about the anonymity and confidentiality of their data, confirming that their participation in the study is voluntary.

To access and play the *emoTICare serious game* online for six weeks (one week per mission of the game), participants will be provided with a link at the end of the evaluation survey conducted at T1. This *serious game* contains six distinct areas, each designed to be completed within a maximum of one week, thus allowing sufficient time to progress at different paces. During the period in which the adolescents are completing the *serious game*, an email address and a mobile phone number will be made available for participants to contact in case they need assistance (see Table 1).

**Table 1 pone.0325763.t001:** Intervention timeline.

				Timeline (in months)																															
	2024							2025												2026												2027			
	Jun	Jul	Aug	Sep	Oct	Nov	Dec	Jan	Feb	Mar	Apr	May	Jun	Jul	Aug	Sep	Oct	Nov	Dec	Jan	Feb	Mar	Apr	May	Jun	Jul	Aug	Sep	Oct	Nov	Dec	Jan	Feb	Mar	Apr

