### Measurements

Missing data will not be an issue, as the survey is conducted through LimeSurvey, where all questions are mandatory and cannot be skipped by participants.

To be included in the data analysis, participants must have completed all three measurement points and answered all questionnaires.

T1: First measurement: After the participant had signed the informed consent, the initial score for this outcome was assessed.T2: Second measurement: POST Up to 6 weeks after the second measurement, the second measurement of the same variable was carried out.T3: Third measurement: POST Up to 6 months after the second measurement, the third measurement of the same variable was carried out.

[Time Frame: Baseline up to 30 weeks]

Primary Outcome Measure:

Change Quality of Life (measured by KIDSCREEN-27).Change Emotional and Behavioral Problems (measured by SDQ).Change Emotional Competences (measured by EAQ-30).Change Self-concept (measured by CAG)Change Coping (measured by SPSI-R).Change Social Skills (measured by CHASO).

Secondary Outcome Measure:

Change Threat of disease (measured by BIP-Q)Change Psychoeducation Diabetes

Psychoeducation of the disease: the ECODI Diabetes knowledge scale will be used to assess this variable [79]. This scale consists of 25 items and four dimensions: basic knowledge and self-care, laboratory values, diet and physical exercise. It is a scale that is corrected by the number of hits and misses.

[Time Frame: Start of the game and during the game]

Change Resilience (measured by CD-RISC).

Other Pre-specified Outcome Measures:

Glycaemic control

HbA1c: It will be used to evaluate the glycemic control of the diabetic patient in endocrinology diseases.

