Secondly, incidental sampling may hinder the generalization of the program’s results, as the sample may not fully represent the wider population of adolescents with Type 1 Diabetes. Thirdly, the online and remote format of the evaluation process, along with the use of the emoTICare program, may present challenges in ensuring proper completion, potentially increasing the likelihood of experimental mortality. Moreover, the online format could impact participant engagement, as the lack of direct interaction may lead to decreased attention or motivation. This is particularly relevant as maintaining participant motivation throughout the study period is a challenge in long-term interventions, and participants may experience fatigue or loss of interest over time. Additionally, biases in self-reported data could arise, as participants might provide socially desirable answers or misinterpret the questions, affecting the accuracy of the data. Conversely, per-protocol analysis (PP) provides a clear understanding of the potential benefits of treatment by focusing on subjects who have completed their assigned treatment regimen. However, it is limited in that it does not account for real-world challenges to adherence in real-world settings.

A further limitation of this study is the absence of specific data on the incidence of type 1 diabetes in individuals under 16 years of age. Instead, the incidence in individuals under 15 was used as a reference. It is acknowledged that this may result in under- or overestimation, owing to the exclusion of data from 15–16-year-olds. It is also noted that, given the relatively narrow additional age span (one year), any deviation in incidence is unlikely to significantly affect the overall power or feasibility estimates of the study. Incidence figures for individuals under 15 years are extensively utilised in international diabetes surveillance and are regarded as robust and comparable across populations. Given that the majority of the target population falls within the 12–14 age range, it was considered reasonable to use incidence data for individuals under 15 years as a proxy for estimating the expected number of eligible participants. Furthermore, the incidence of type 1 diabetes between ages 15 and 16 does not markedly deviate from that observed in the immediately preceding years, particularly in populations with relatively stable incidence curves.

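### The careless-answering rule names no wave, so with the all-three-waves rule it can exclude adolescents after randomisation for how they answer at T2 or T3

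*Protocol article*

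**What the plan says.** Under Assessment tools (Psychological variables), the protocol article describes the infrequency scale: "This scale consists of 12 Likert-type items (1–5) that are distributed throughout the questionnaire at key points". The consequence of failing it is: "If a subject answers three or more items incorrectly, their questionnaire responses will be invalidated". The sentence does not say at which wave the rule applies, or whether it voids one wave or all of that person's data.

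The Study design section repeats the evaluation in both arms after six weeks ("a second evaluation (T2) of all participating adolescents (control and experimental groups) will take place") and again six months later. For the experimental arm, game access follows the baseline survey: "participants will be provided with a link at the end of the evaluation survey conducted at T1". T2 and T3 therefore come after allocation.

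The Measurements section sets the condition for analysis: "To be included in the data analysis, participants must have completed all three measurement points and answered all questionnaires". It also states: "Missing data will not be an issue, as the survey is conducted through LimeSurvey, where all questions are mandatory".

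The Data analysis section adds a per-protocol main analysis, last observation carried forward (LOCF) for missing values, sensitivity analyses for missing data that are not described further, and a chi-square comparison between arms of the numbers who withdraw.

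**The concern.** A participant can complete all six missions and all three surveys and still lose a questionnaire to the infrequency rule. If a voided survey counts as not completed, the Measurements rule then drops that person, including a valid T1 and any other valid wave. This exclusion depends on behaviour after randomisation. It is separate from the adherence and withdrawal exclusions, so changing the per-protocol choice alone would not remove it.

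Attention at T2 and T3 may differ by arm. One arm has just finished six weeks of a game designed to engage; the waiting list has had no activity and answers the same long battery again. Inattention may also be related to the self-reported outcomes. Removing inattentive responders could then unbalance the arms, in a direction that cannot be known beforehand.

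The statement that missing data will not arise is also wrong on the plan's own terms. Mandatory fields prevent blank items, but the infrequency rule removes completed questionnaires.

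**Working it through.** **What happens to a voided T2 or T3.** Three readings can be set side by side:

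1. Measurements, natural reading: a voided wave is not a completed wave, so the participant leaves the analysis.
2. Measurements, literal reading: the survey was filled in, so the participant stays but has no usable data at that wave.
3. Data analysis, LOCF: a voided T2 takes the T1 value, so the T2 minus T1 change used in the hierarchical regression is exactly 0. A voided T3 takes the T2 value.

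The article does not choose between them. None is harmless: the first selects after randomisation, the second leaves an unaddressed gap, and the third enters a made-up change score.

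**Whether the plan would notice.** The attrition chi-square counts withdrawals. A voided participant has not withdrawn and does not appear in it.

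**Size.** Inputs from the Sample size section are total 372 and dropout 20%. The 372 is taken as stated; it does not follow from the listed ingredients. The margin-of-error formula with 90,000 people gives 383 before dropout. A two-arm comparison at an assumed d = 0.5 with 80% power and 20% dropout gives 158. The present point does not depend on this.

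The careless-response rate p per wave is not given. Assumed values are 3%, 5% and 10%, independent between waves. Only T2 and T3 are counted, because the concern is voiding at the outcome visits.

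- Remaining after dropout: 372 × 0.80 = 297.6, about 298.
- Share of otherwise complete participants lost: 1 − (1 − p)².
- Evaluable: 297.6 × (1 − p)².

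| p per wave | Lost | Evaluable |
|---|---|---|
| 3% | 1 − 0.97² = 5.9% | 280 |
| 5% | 1 − 0.95² = 9.75% | 269 |
| 10% | 1 − 0.90² = 19.0% | 241 |

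**Power.** With n per arm equal to half the evaluable number and a two-sided 5% level, power is approximately Φ(d√(n/2) − 1.96). The article calls the effect moderate without a number, so d = 0.5 is assumed and d = 0.3 shown as a lower case. At d = 0.5, power is 99% with 298 evaluable and 97% with 241. At d = 0.3, it falls from 73% to 71%, 69% and 64% for the three rates.

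**What an arm difference would look like (illustration only).** Suppose p is 10% in one arm and 3% in the other. Each arm has 297.6 / 2 = 148.8 after dropout. One keeps 148.8 × 0.81 = 120.5 and the other 148.8 × 0.9409 = 140.0. About 28 and 9 participants are removed, and the withdrawal comparison shows none of it.

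**The case against.** The strongest objection is that the chain is inferred. The article does not say outright that the infrequency items are given at T2 and T3, that invalidation is scored by wave, or that a voided wave counts as not completed. This stands as a limit on how firmly the point can be put. It does not remove the point: the items sit inside a battery that is repeated, the rule carries no restriction, and both rules are stated rather than left open.

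A reader might infer that one careless outcome survey removes the adolescent from every analysis. The article does not support that. LOCF and the missing-data sensitivity analyses could retain the person, and baseline comparisons might too.

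A reader might also count three waves and obtain losses of 9%, 14% and 27%. That includes T1, which is not part of the harm described here. Nor is the repeated battery shown to have 248 items: that total includes 25 diabetes-knowledge items with their own time frame, tied to the start and course of the game. Without them the count is 223. The Discussion does not predict fatigue; it says "participants may experience fatigue or loss of interest over time", and it does not mention careless answering.

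Finally, the threshold is prespecified and identical in both arms, and keeping flagged answers could itself let arm-dependent invalid data into the estimate. That is fair. It is a reason to analyse both ways, and not to assume that retention only adds noise. Turning the rule into a T1 eligibility screen would change who is randomised and is likewise a debatable choice, so it is not asked for here.

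**Conclusion.** The point holds as a defect in how the rules combine. The infrequency rule has no stated wave or scope, the inclusion rule demands all three waves, and the LOCF provision points the other way. On the natural reading, randomised adolescents are excluded for how they answered at an outcome visit, and the attrition check cannot detect a difference between arms. The statement on missing data is contradicted by the infrequency rule itself.

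Under assumed careless rates of 3% to 10% per wave, the loss is about 6% to 19% of otherwise complete participants, on top of the stated 20% dropout. The rates and the independence between waves are assumptions; if carelessness clusters in the same people, fewer are lost. Power is barely touched at d = 0.5 and moderately reduced at d = 0.3, so selection is the main concern. The direction of any bias is unknown. This should be corrected before outcome data are analysed.

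**What to change.** Reconcile the Psychological variables, Measurements and Data analysis sections as follows:

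- State at which waves the infrequency scale is scored, and that a flagged T2 or T3 voids that wave only. Amend the all-three-waves condition so that the participant is not removed and the other valid waves stay in the analysis.
- State how the voided wave is handled, so that it is not left open between exclusion and LOCF.
- Report the number flagged by arm and wave, and add these counts to the attrition comparison beside withdrawals.
- Run the main comparison with and without flagged waves, and prespecify which is primary.
- Delete the sentence saying that missing data will not be an issue.

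The cost is a few sentences, one extra analysis and some incomplete cases to handle. Data collection does not change.
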